## Abstract

**Background:**

Most recent childhood invasive pneumococcal disease in the UK is caused by serotypes not included in the currently used pneumococcal conjugate vaccine (PCV13). There is potential for additional protection with newer PCVs that have wider serotype coverage but there are no data on these vaccines being given in the 1+1 schedule used in the UK. This study will determine whether the PCV13 serotype-specific antibody responses to PCV15 and PCV20 given at 3 and 12 months (1+1 schedule) are non-inferior to PCV13 serotype-specific antibody responses to PCV13 given in the same schedule. It will also determine whether PCV13 serotype-specific antibody responses to PCV20 given at 2, 4 and 12 months (2+1 schedule) are non-inferior to PCV13 serotype-specific antibody response to PCV13 given at 3 and 12 months (1+1 schedule).

**Methods:**

This will be an open-label, randomised controlled multicentre study in 600 infants. Healthy infants will be enrolled at 8 weeks and randomised 1:1:1:1 to receive 2 doses (1+1) of either PCV15, PCV20 or PCV13 at 3 and 12 months of age or 3 doses (2+1) of PCV20 at 2, 4 and 12 months. Blood and nasal samples will be collected at specified intervals to assess serum and nasal IgG levels and carriage. Postprimary and postbooster IgG levels in the PCV15 and PCV20 arms will be compared against PCV13.

**Ethics and dissemination:**

Ethical approval for this study has been obtained from the South Central—Hampshire A Research Ethics Committee (REC ref 24/SC/0222). The results will be disseminated via publication in a peer-reviewed journal and presentations at international conferences.

**Trial registration number:**

ISRCTN17673117.

STRENGTHS AND LIMITATIONS OF THIS STUDYThe study specifically evaluates the 1+1 schedule for which no immunogenicity data currently exist for pneumococcal conjugate vaccine (PCV15) or PCV20 in infants, addressing an important evidence gap.The open-label design may introduce reporting bias for reactogenicity.The study sample size is not sufficient to give data on vaccine efficacy.

## Introduction

### Background and rationale

*Streptococcus pneumoniae* causes pneumonia and invasive pneumococcal disease (IPD), including sepsis and meningitis, especially in children and older adults.^1
2^ There were 378 cases of IPD among children aged 0–14 years in the UK from April 2022 to March 2023.^1^
*S. pneumoniae* commonly colonises the nasopharynx of healthy young children, and asymptomatic pneumococcal carriage has been observed in nearly half of children aged 1–2 years in a study within the Thames Valley region of the UK.^3^ However, nasopharyngeal carriage is also a precursor to disease and transmission.^4^ There are at least 100 serotypes of *S. pneumoniae*,^5^ which have varying capacities to cause disease.^6^ Immunity derived from pneumococcal conjugate vaccine (PCV) tends to be serotype specific with little or no crossover.^7^

Since the UK introduced the seven-valent PCV7, containing serotypes 4, 6B, 9V, 14, 18C, 19F and 23F, in 2006, childhood IPD caused by vaccine serotypes has declined.^1^ In 2010, the UK switched from PCV7 to PCV13, which includes six additional serotypes (4, 6B, 9V, 14, 18C, 19F and 23F). PCV13 was introduced in a 2+1 schedule (two priming doses and a booster) and was later changed to a 1+1 schedule (priming and booster doses at 3 and 12 months) in 2020. This decision was based on findings from a postlicensure trial that demonstrated non-inferior postbooster immunogenicity of 1+1 compared with the 2+1 schedule.^8^ Vaccine failure or breakthrough infections have not increased since switching to the reduced schedule; however, approximately 80% of childhood IPD in the UK is now caused by non-PCV13 serotypes.^1^ Similarly, the predominance of non-PCV13 serotypes was observed in healthy carriage among vaccinated children.^3^ This evidence supports the need to assess whether switching to any of the new higher-valency PCVs with wider serotype coverage could further reduce childhood IPD.

In addition to PCV13 serotypes, PCV15 and PCV20 include two (22F and 33F) and seven (8, 10A, 11A, 12F, 15B, 22F and 33F) other serotypes, which account for an additional 13% and 42% of childhood IPD, respectively.^1^

PCV15 and PCV20 were recently approved for use in infants in the USA^9^ and the EU,^10
11^ based on non-inferiority of immunogenicity to PCV13 for the PCV13-shared serotypes.^12
13^ The European Medicines Agency licensed PCV13 and PCV15 in a 2+1 schedule whereas PCV20 was licensed in a 3+1 schedule, as it failed to achieve non-inferiority of immunogenicity to PCV13, after a 2+1 schedule.^14^ PCV15 was licensed in the UK by the Medicines and Healthcare products Regulatory Agency (MHRA) in 2022 for use from 6 weeks of age in a 1+1 schedule^15^ while PCV20 (APEXXNAR/PREVENAR 20) has been licensed in the UK from 24 September 2024 as a 2+1 and 3+1 schedule from 6 weeks to 15 months of age. Although non-inferiority criteria were not met for some serotypes in PCV20, licensing decisions were based on the overall evidence, including safety, immunogenicity and expanded serotype coverage. Both of these vaccines are not yet part of the routine immunisation schedule. PCV13 continues to be used in the childhood immunisation programme.^16^ There is no real-world evidence on the efficacy of PCV15 and PCV20 against childhood IPD or carriage. Although PCV15 and PCV20 may reduce IPD caused by non-PCV13 serotypes, the reduction in individual serotype immunogenicity with increasing valency makes it uncertain whether either vaccine would have a greater impact on overall IPD than PCV13, especially if used in a reduced schedule.^17
18^ In fact, predictions from a modelling study suggest a possible increase in IPD following a switch from PCV13 to PCV15 because the anticipated gains from eliminating the two additional serotypes could be nullified by a predicted replacement with more invasive non-PCV15 serotypes.^18^

These uncertainties about the potential impact of new PCVs provide justification for comparing the immunogenicity of PCV15 and PCV20 against PCV13, at the reduced schedule currently used in the UK. Evidence generated from a head-to-head comparison of these PCVs would inform decisions on the UK PCV schedules.

### Study aims and objectives

This study aims to compare the immunogenicity and safety of PCV15 and PCV20 vaccines when administered in different dosing schedules with PCV13 vaccine as the control. The study comprises four arms. Participants in arms 1, 2 and 4 receive a two-dose schedule of PCV15, PCV20 and PCV13, respectively, at 3 and 12 months of age, whereas participants in arm 3 receive a three-dose schedule of PCV20 at 2, 4 and 12 months of age. Primary, secondary and exploratory objectives and outcomes are outlined in table 1.

**Table 1 T1:** Primary, secondary and exploratory objectives and outcomes of PCV15/PCV20 study

Objectives	Outcome measures
Primary objective*:* To determine if the PCV13 serotype-specific serum IgG concentrations are non-inferior in homologous arms 1 and 2 in comparison to the control arm 4.	PCV13 serotype-specific serum IgG concentration at 13 months of age.
Secondary objectives: To determine if the PCV13 serotype-specific serum IgG concentrations are non-inferior in arm 3 in comparison to the control arm 4.	PCV13 serotype-specific serum IgG concentration at 13 months of age.
To characterise the seven additional PCV20 serotype-specific serum IgG concentrations following homologous PCV schedules.	PCV20 serotype-specific serum IgG concentrations (Serotypes 8, 10A, 11A, 12F, 15B, 22F and 33F) at 13 months of age.
To determine the safety and reactogenicity of different schedules with PCV15 (1+1) and PCV20 (1+1) and (2+1).	Solicited AEs within 7 days Unsolicited AEs within 28 days *SAEs during the whole study period.
Exploratory objectives: To determine if the vaccine induces IgG response at the mucosa (nasal) and if antibody levels in the nose correlate with levels in blood.	PCV13 serotype specific nasal IgG GMC against some of the PCV serotypes (sample volume depending) at 13 months of age.
To determine the PCV20 serotype-specific IgG concentration following one dose of PCV13, PCV15 or PCV20.	PCV20 serotype-specific serum IgG concentrations at 4 months.
To determine the PCV20 serotype-specific IgG concentration following two doses of PCV20 (2+1) schedule.	PCV20 serotype-specific serum IgG concentrations at 5 months.
To detect pneumococcal colonisation and serotype present.	Molecular microbiology (fluidic qPCR for detection of lytA, paiB and serotyping) at 13 months of age.
To determine immunogenicity against concomitant vaccines given as part of the infant routine immunisation schedule.	IgG antibody GMCs concentration against pertussis antigen (pertussis toxin, filamentous haemagglutinin and pertactin), diphtheria toxoid, tetanus toxin and Hib capsular polysaccharide; SBA GMT against MenB at 13 months of age.

AEs, adverse events; GMC, geometric mean concentrations; PCV, pneumococcal conjugate vaccine; SAEs, Severe Adverse Effects; SBA GMT, serum bactericidal antibody (SBA) geometric mean titres (GMTs).

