### Protocol amendment affecting PCV schedule

From 1 July 2025, during study enrolment, the national immunisation schedule changed with the second dose of MenB now given at 3 months (previously 4 months) and in consequence the first dose of PCV was to be given at 4 months (previously 3 months). In order to provide some data on the revised schedule for the broader valency PCV vaccines, a substantial amendment was submitted (substantial amendment 3.0: 16 May 2025, approved 24 June 2025) which included comparing the effect of giving the single PCV dose at 3 vs 4 months. This introduced a second randomisation for arms 1, 2 and 4 allocating participants within these arms to receive PCV at 3 or 4 months with the blood sample 1 month after either time point (see online supplemental document: major protocol amendment). The primary endpoint was unchanged by this amendment. At the point of implementation of this amendment 237 infants had already been enrolled into the study. A complete amendment history is provided as online supplemental material.

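### The exploratory one-dose IgG outcome is still fixed at 4 months of age, which is the age of the first dose for infants whom the amendment randomises to priming at 4 months

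*Protocol article*

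**What the plan says.** Table 1, under Study aims and objectives, has two exploratory post-priming rows for serum IgG.

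- One dose. The objective is "To determine the PCV20 serotype-specific IgG concentration following one dose of PCV13, PCV15 or PCV20" and the outcome is "PCV20 serotype-specific serum IgG concentrations at 4 months".
- Two doses. The objective is "To determine the PCV20 serotype-specific IgG concentration following two doses of PCV20 (2+1) schedule" and the outcome is "PCV20 serotype-specific serum IgG concentrations at 5 months".

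Table 2, under Study timeline, has the same layout. Before the booster, arms 1, 2 and 4 are bled only at V3 (4 months). The 5-month visit, V3(A), shows a blood sample for arm 3 only.

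The section Protocol amendment affecting PCV schedule describes an approved change to arms 1, 2 and 4. A second randomisation was added, "allocating participants within these arms to receive PCV at 3 or 4 months with the blood sample 1 month after either time point". Its stated aim includes "comparing the effect of giving the single PCV dose at 3 vs 4 months". The section also says: "The primary endpoint was unchanged by this amendment". By the time the change took effect, 237 infants had been enrolled.

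The abstract announces that "Postprimary and postbooster IgG levels in the PCV15 and PCV20 arms will be compared against PCV13".

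**The concern.** The one-dose objective concerns the response to a dose, but its outcome is tied to an age. While every infant in arms 1, 2 and 4 was primed at 3 months, the two were the same thing: 4 months of age was 1 month after the dose. The second randomisation separates them. For infants primed at 4 months, the age in Table 1 is when the first dose is given, and the sample that measures the response comes about a month later.

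At stake is whether the infants whom the amendment set out to study appear in the outcome that most directly measures the effect of priming age. Table 1 also lists no outcome for the 3 versus 4 month comparison, so a reader cannot tell from the outcome table which measurement will carry it.

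**Working it through.** **Is this current text?** Yes. The amendment section is part of the Methods and describes the design in force. It is not a log of superseded wording. Tables 1 and 2 still carry the timing that applied before it.

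**Timing in arms 1, 2 and 4.** Age at blood sample = age at first PCV dose + 1 month.

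| Randomised priming age | Age at post-dose blood sample | Table 1, one-dose outcome | Table 2, blood sample before the booster |
|---|---|---|---|
| 3 months | 3 + 1 = 4 months | 4 months: agrees | V3, 4 months: agrees |
| 4 months | 4 + 1 = 5 months | 4 months: the age of the dose | V3, 4 months only: does not agree |

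The 5-month age is derived from the sampling interval in the amendment section; the article does not print it for these arms.

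**How many infants.** Inputs: 600 infants in total and 150 per arm (Study design), 1:1:1:1 allocation (Randomisation), and 237 enrolled before the change (amendment section). The ratio of the second randomisation is not given, so it is varied.

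- Later enrolments: 600 − 237 = 363.
- Per arm, if the 237 were spread evenly: 363 / 4 = 90.75. Across arms 1, 2 and 4: 3 × 90.75 = 272.25.

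| Assumed ratio, 3 months : 4 months | Primed at 4 months, per arm | Share of 150 | Across arms 1, 2 and 4 |
|---|---|---|---|
| 2:1 | 90.75 × 1/3 = 30.25 | 20% | 91 |
| 1:1 | 90.75 × 1/2 = 45.4 | 30% | 136 |
| 1:2 | 90.75 × 2/3 = 60.5 | 40% | 182 |

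These are enrolled infants, before attrition. They assume that all 363 later infants, and none of the first 237, enter the second randomisation.

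**The plan's own sample size.** With SD 0.5 on the log10 scale, margin −log10(0.67) = 0.1739, one-sided 0.025 and 80% power, n = 2 × (1.960 + 0.842)² × 0.5² / 0.1739² ≈ 130 per arm, against 131 stated. The figure is reproduced. It belongs to the 13-month comparison and does not depend on the post-priming time point.

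**The case against.** The best defence is that the amendment section already gives the dose-relative rule: it schedules blood 1 month after whichever priming age was allocated and says why. On that reading Table 1 describes the design before the change, and the later section modifies it. The article also refers to a supplementary amendment document, not shown here, which may define the time point correctly. And the outcome is exploratory, with no margin or power attached.

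Much of this stands. The samples are scheduled, and a careful analyst would probably use them. It cannot be said that the full protocol has the error. But the article prints a specific time point in its outcome table, and that time point conflicts with its own description of the design. This is not a detail left to another document.

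Three stronger readings are tempting, and the documents do not support them.

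- A reader might infer that one-dose samples taken at 5 months would be mixed into the two-dose outcome, since both fall at the same age. The two-dose row is limited by its objective to two doses of PCV20 in the 2+1 schedule, which is arm 3. Only the age coincides, and no analysis by age across arms is described.
- A reader might infer that the 3 versus 4 month comparison cannot be made. The amendment section states that comparison and schedules its blood sample. What is missing is a matching entry in Table 1.
- A reader might count the omitted infants as lost precision that a correction would restore. Comparing arms within priming age leaves the 3-month comparison with the same infants as the literal reading. It adds a second stratum; only a pooled estimate would use everyone.

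**Conclusion.** The point holds as a contradiction between an exploratory outcome definition and the amended design. For infants primed at 4 months, Table 1 names the age of the first dose as the time to measure the response to it, and Table 2 does not show the sample that the amendment section schedules. Taken literally, the one-dose outcome omits about 45 infants per arm (30%), with a range of 20% to 40%. That size rests on an assumed ratio between 2:1 and 1:2, an even spread of the first 237 infants over the arms, and a second randomisation that covers exactly the 363 later enrolments.

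The effect stops at the exploratory post-priming outcomes. The 13-month primary and secondary IgG outcomes and the sample size are unaffected. It should be corrected before analysis but does not threaten the main conclusions. No view is taken on the age at which the first dose should be given.

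**What to change.** Reconcile Tables 1 and 2 with the amendment section.

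- **Table 1, one-dose outcome:** define it as serum IgG 1 month after the first PCV dose in arms 1, 2 and 4, derived from the recorded dose date and not from age or visit label.
- **Analysis of that outcome:** compare arms within randomised priming age. A pooled estimate adjusted for priming age may be added.
- **3 versus 4 month comparison:** list it in Table 1 on this outcome. The randomised contrast rests on the infants who went through the second randomisation, because those primed before it were not allocated a priming age.
- **Table 1, two-dose outcome:** for clarity, label it as 1 month after the second PCV20 dose, arm 3.
- **Table 2:** make the blood-sampling rows for arms 1, 2 and 4 agree with the amendment section.

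The cost is a few reworded table entries and a derivation keyed to the dose date. No samples, visits or sample-size changes are needed. The drawback is that one-dose results will come from two ages and must be shown separately, with smaller numbers in each part.

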## Methods

### Study design

This is an open-label, randomised controlled, multicentre study with a sample size of 600 participants recruited and assigned to four arms of 150 participants each.

### Study timeline

Healthy children are enrolled at approximately 2 months (+2 weeks) of age. Participants in arms 1, 2 and 4 will receive two doses of either PCV15, PCV20 or PCV13 at 3 and 12 months of age, while arm 3 will follow a 2+1 schedule and will receive two doses of PCV20 at 2 months and 4 months, followed by a booster dose at 12 months. Blood and nasal samples will be collected throughout the study according to the allocated study arm, and the time points for each have been specified in table 2.

**Table 2 T2:** Study schedule for vaccines and sampling

Visit number	V1	V2	V3	V3 (A)	V4	V5
Participant age	2 months	3 months	4 months	5 months	12 months	13 months +
Blood sample for arms 1, 2, and 4	–	–	Yes		–	Yes
Blood sample for arm 3				Yes		Yes
Nasal sample (mucosal lining fluid) for arms 1, 2 and 4		Yes	Yes		–	Yes
Nasal sample (mucosal lining fluid) for arm 3	Yes	Yes		Yes		Yes
Routine vaccines arms 1–4	6:1 MenB Rotavirus	6:1 Rotavirus	6:1 MenB		MenB Hib/MenC MMR	–
Pneumococcal vaccines arm 1	–	PCV15	–		PCV15	–
Arm 2	–	PCV20	–		PCV20	–
Arm 3	PCV20		PCV20		PCV20	–
Arm 4	–	PCV13	–		PCV13	–

MMR, Measles Mumps Rubella; PCV, pneumococcal conjugate vaccine.

This study opened to recruitment from 3 December 2024, when the first participant was enrolled. Recruitment is expected to be completed by October 2026.

### Protocol amendment affecting PCV schedule

From 1 July 2025, during study enrolment, the national immunisation schedule changed with the second dose of MenB now given at 3 months (previously 4 months) and in consequence the first dose of PCV was to be given at 4 months (previously 3 months). In order to provide some data on the revised schedule for the broader valency PCV vaccines, a substantial amendment was submitted (substantial amendment 3.0: 16 May 2025, approved 24 June 2025) which included comparing the effect of giving the single PCV dose at 3 vs 4 months. This introduced a second randomisation for arms 1, 2 and 4 allocating participants within these arms to receive PCV at 3 or 4 months with the blood sample 1 month after either time point (see online supplemental document: major protocol amendment). The primary endpoint was unchanged by this amendment. At the point of implementation of this amendment 237 infants had already been enrolled into the study. A complete amendment history is provided as online supplemental material.

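### The 1+1 arms are still described as 3 and 12 months, but since the amendment they mix first doses at 3 and 4 months; the whole-arm comparison and its 80% power belong to that pooled schedule

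*Protocol article*

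**What the plan says.** All places are in the Protocol article.

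**Schedule stated as 3 and 12 months.** The Abstract (Background) frames the primary question as whether "antibody responses to PCV15 and PCV20 given at 3 and 12 months (1+1 schedule) are non-inferior" to PCV13 in the same schedule. It sets the arm 3 question against the "PCV13 serotype-specific antibody response to PCV13 given at 3 and 12 months (1+1 schedule"). The Abstract (Methods) has infants randomised "to receive 2 doses (1+1) of either PCV15, PCV20 or PCV13 at 3 and 12 months of age". Study aims and objectives, Study timeline and Table 2 repeat this for arms 1, 2 and 4. Investigational medical products limits PCV13 to those two ages exclusively and gives them as the UK routine schedule. Randomisation refers the reader back to Table 2.

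**Schedule stated as 3 or 4 months.** Protocol amendment affecting PCV schedule reports that from 1 July 2025 MenB moved and "in consequence the first dose of PCV was to be given at 4 months (previously 3 months"). The amendment, approved on 24 June 2025, "included comparing the effect of giving the single PCV dose at 3 vs 4 months" and did so by randomisation: "This introduced a second randomisation for arms 1, 2 and 4 allocating participants within these arms to receive PCV at 3 or 4 months". At implementation 237 infants had been enrolled. The section adds: "The primary endpoint was unchanged by this amendment".

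**Analysis and sample size.** The Table 1 primary objective, the hypotheses in Statistical analysis and the 131 evaluable infants per arm in Sample size are all defined by arm and name no priming age. The regression lists site as the only randomisation design variable.

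**The concern.** The two descriptions cannot both be true of the trial being run. The amendment section describes the current design, so the 3-and-12-month text is what has fallen out of date. The statement that PCV13 is given at those two ages and no others fails for every control infant assigned to 4 months.

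The assurance about the endpoint does not settle this. The endpoint is IgG at 13 months, and it is indeed the same. What changed is the pair of schedules being compared. A whole-arm analysis now averages over two priming ages, while the stated question names one. The arm 3 question has the same mismatch, because its reference is the same mixed arm 4.

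At stake is how the result is labelled. A whole-arm ratio reported under a 3+12 heading would describe a schedule that part of each 1+1 arm did not follow, and the 80% power could be read as applying to 3+12.

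**Working it through.** **Step 1: reproduce the plan's figure.** Inputs from Sample size and Statistical analysis: SD 0.5 on the log10 scale, ratio margin 0.67, two-sided 0.05 (one-sided 0.025), true ratio 1. The margin is log10(0.67) = -0.1739. With n per arm, the non-centrality is 0.1739 / (0.5 × √(2/n)) on 2n - 2 degrees of freedom.
- n = 130: power 79.8%.
- n = 131: power 80.1%. The stated 131 reproduces.
- 150 recruited less 15% to 10% attrition = 127.5 to 135: power 79.0% to 81.3%.

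So the 80% needs the whole arm.

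**Step 2: how mixed are the arms?** The article does not give the ratio of the second randomisation, nor say what happened to infants enrolled but not yet primed when the amendment took effect. Assume that the 237 divide evenly over four arms, that all were primed at 3 months, and that the later split is 1:1.
- Before the amendment: 237/4 = 59.25 per arm. After: 150 - 59.25 = 90.75 per arm.
- Primed at 4 months: 90.75/2 = 45.4, which is 45.4/150 = 30% of the arm.
- Primed at 3 months: 59.25 + 45.4 = 104.6.

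**Step 3: power by schedule, per serotype, same formula.** The 1:1 column is the main assumption. The other two vary the later split (3 months : 4 months).

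| Comparison | 1:1 | 2:1 | 1:2 |
|---|---|---|---|
| Share primed at 4 months | 30% | 20% | 40% |
| Pooled, 127.5-135 evaluable | 79-81% | 79-81% | 79-81% |
| 3+12 alone: evaluable per arm | 88.9-94.2 | 101.8-107.8 | 76.1-80.6 |
| 3+12 alone: power | 64-66% | 69-72% | 57-59% |
| 4+12 alone: evaluable per arm | 38.6-40.8 | 25.7-27.2 | 51.4-54.5 |
| 4+12 alone: power | 33-34% | 23-24% | 42-44% |

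These ranges vary only the later split. If some of the 237 joined the second randomisation, the share at 4 months would be larger and the figures would move further.

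**Step 4: does pooling cost power?** If priming age shifts log10 IgG by δ equally for all vaccines, leaving it out of the model raises the SD to √(0.25 + s(1 - s)δ²), with s the share primed at 4 months.
- s = 0.3025, δ = 0.1: SD 0.502, power at 131 per arm 79.8%.
- s = 0.3025, δ = 0.2: SD 0.508, power 78.8%.
- s = 0.403, δ = 0.2: SD 0.510, power 78.6%.

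The loss is at most about 1.5 points. Pooling changes the question answered, hardly the power.

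**The case against.** The best defence is that the change is disclosed. The amendment has its own headed Methods section, directly after the study timeline, with dates, arms affected, the second randomisation and the number already enrolled, and it points to a supplement that is not shown here. The split ratio and the handling of priming age may properly sit in that supplement or in the analysis plan, and their absence is no fault. The formal objective, hypotheses and sample size name no age and agree with one another, and the 131 reproduces. All of this stands. It narrows the point to the schedule label, but it does not make the 3-and-12-month statements true, and no supplement could.

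The power figures for single schedules rebut nothing that the article claims, since it attaches 80% to arms and does not call either schedule's own comparison primary. That also stands, so they serve only as context.

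Three stronger readings may tempt a reader:
- **That the primary comparison is biased.** Vaccine allocation is randomised, and priming age is then randomised within each of these arms. Provided the split is the same across them, the pooled contrast is fair.
- **That pooling inflates false claims of non-inferiority for 3+12.** This needs the vaccine ratio to differ by priming age, and the documents give no figure for such an interaction.
- **That the trial no longer meets its rationale of** "comparing the immunogenicity of PCV15 and PCV20 against PCV13, at the reduced schedule currently used in the UK". There the reduced schedule most naturally means 1+1, and a first dose at 4 months is still 1+1.

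**Conclusion.** The point holds as a conflict in the current text about which schedule is being compared. The whole-arm objective, hypotheses and sample size address a 1+1 schedule with first dose at 3 or 4 months, and about 80% power belongs to that pooled comparison. The abstract's primary question, its arm 3 question, the arm descriptions, Table 2 and the PCV13 product statement still say 3 and 12 months.

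The trial is not invalidated, and the pooled comparison is not underpowered. The article does not say outright that the primary analysis pools; this follows from its arm-level wording and sample size. If it were instead restricted to 3+12, power would be about 64-66% under the assumptions above (57-72% over the splits examined), and the stated 80% would not be met. The 30% share and the single-schedule powers depend on an unstated 1:1 split and on all 237 having been primed at 3 months. The mislabelling itself depends on neither.

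This should be fixed: the correction is cheap and governs how the main result will be read.

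**What to change.** 1. State the primary comparison, and the arm 3 versus arm 4 comparison, as using 1+1 arms with the first dose at 3 or 4 months as assigned, pooled. Attach the 80% power to that. The hypotheses need no change beyond the arm definition.
2. Bring the Abstract (Background and Methods), Study aims and objectives, Study timeline and Table 2 into line with the amendment section. In Investigational medical products, remove the restriction of PCV13 to 3 and 12 months and update the sentence on the UK routine schedule.
3. In Statistical analysis, add assigned priming age to the model for comparisons among arms 1, 2 and 4, because it is now a randomised factor. The gain in power is small (Step 4). A term for enrolment before or after the amendment is optional for the vaccine contrast. It matters mainly for comparing 3 with 4 months, since the second randomisation began only after 237 infants had been enrolled.
4. Report 3+12 and 4+12 estimates as supportive, and say that their power is lower.

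The cost is wording and one model term, with no extra infants or visits. The sponsor must accept that the 80% covers the pooled question only.
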